## Abstract

**Background:**

Due to a rapidly ageing population in the world, it is increasingly pertinent to promote successful ageing strategies which are cost-effective, easily accessible, and more likely to be acceptable to the elderly. Past research associates exposure to natural environments and horticultural therapy (HT) with positive psychological, social and physical health benefits. This Randomized Controlled Trial (RCT) is designed to evaluate the efficacy of HT in promoting Asian elderly’ mental health, cognitive functioning and physical health.

**Methods/design:**

70 elderly participants aged 60 to 85 years old will be randomized to participate in either the active horticultural therapy group or be in the waitlist control. Sessions will be weekly for 12 weeks, and monthly for 3 months. Mental health will be assessed through self-reports of depressive and anxiety symptomatology, life satisfaction, social connectedness and psychological well-being, collaborated with immunological markers. Outcome measures of cognitive functioning and physical health include neuropsychological tests of cognitive function and basic health screening. Outcomes will be assessed at baseline, 3 months and 6 months post-intervention.

**Discussion:**

This RCT comprehensively investigates the efficacy of a non-invasive intervention, HT, in enhancing mental health, cognitive functioning and physical health. The results have tremendous potential for supporting future successful ageing programs and applicability to larger populations.

**Trial registration:**

ClinicalTrials.gov NCT02495194. Trial registration date: July 13, 2015. Retrospectively registered.

## Background

Worldwide, one in every nine people is aged 60 years and above, and by 2050 the proportion is expected to increase to one in every 5 people [1]. In Singapore, there was a 2.2% increase in the proportion of older persons aged 65 years and above in the recent 5 years [2]. This population has greater mental health risks due to perceived social isolation [3]. Amongst the older adults, gardening is a popular leisure-time activity and exposure to nature has been found to increase positive affect and reduction in anger in individuals, as opposed to those in the urban environment [4]. This may be due to the restorative effects of nature, such as recovery of directed attention fatigue and stress mitigation [5]. Therefore in recent years, there is burgeoning research on therapies which tap on the nature’s benefits on human health and one of which is horticulture.

Definitions of horticultural activities in literature vary in scope from a broad perspective encompassing all forms of exposure to nature and plants, to a more narrow focus on active engagement with plants. Defined broadly, horticultural activities have been shown to reduce depression severity and rumination in clinically depressed patients as the garden environment offers a respite from the urban settings and fascination to them [6]. Notably, besides reducing negative mood (i.e. tension, depression, fatigue, anger and confusion), horticulture also brings about an increase in positive dimension (i.e. vigor/energy) [7]. Similarly, a 7-week indoor horticulture activity program was found to improve participants’ psychological well-being, as compared to the waitlist control group [8]. Hence, horticultural activities may be a promising intervention in improving mental health.

An investigation on the efficacy of horticultural activities in improving mental health, cognitive functioning and physical health is merited for its wider implications. If proven to be effective, this innovative and cost-effective intervention could be a nation-wide strategy in health promotion. It has been stated that the healthcare system alone may be limited in promoting public health [9] and that there is a need for public health strategies to focus on the socio-ecological aspects of health [10]. Therefore, urban parks, which are easily accessible for community-dwelling individuals, are an ideal resource to support the promotion of these aspects of well-being.

Because the present study is a goal-oriented intervention which seeks to enhance the mental, cognitive and physical health of the elderly participants, the definition put forth is adopted:

“Horticultural therapy (HT) is a professionally conducted client-centered treatment modality that utilizes horticulture activities to meet specific therapeutic or rehabilitative goals of its participants. The focus is to maximize social, cognitive, physical and/or psychological functioning and/or to enhance general health and wellness (p. 5).” [11].

Enhanced with the environmental benefits offered by the nature, HT may be a promising intervention in promoting public health and critical in prevention work. However, there is currently a paucity of research on the effectiveness of HT in a multi-ethnic Singaporean population as most studies were conducted either on western societies [6, 12, 13] or Japan and Korea [14]. Due to unique social and cultural specificities, it is inappropriate to assume that the findings could be generalized to our local population.

Furthermore, there are limitations in the existing research. Most of the other studies either have small sample sizes [15–17], short intervention duration [8, 18], or employed the sole use of questionnaires without collaborating evidence from biological data. In addition, a systematic review found that the randomized controlled trials (RCT) conducted thus far have poor methodological and reporting quality [19]. Further research is therefore needed to determine the effectiveness of HT in improving the health of the elderly in the multi-ethnic Singaporean community.

Therefore the aims of this study are to investigate the effectiveness of HT in improving the mental, cognitive and physical health of the community-dwelling older adults using a RCT design. Based on the existing literature, it was hypothesized that, as compared to the waitlist control, participants in the active treatment group will 1) have better mental health, 3) have greater improvement of cognitive functioning and 3) have better physical health. In order to have collaborative evidence with measures of psychological health, the immunology of participants will be investigated via blood-based biomarkers. Notably, past research has found that depressive symptomatology was associated with elevated levels of pro-inflammatory cytokines [20] and lower levels of trophic factor [21].

## Methods

All procedures involved in this trial will be conducted in compliance with the Helsinki declaration and Singapore Guidelines for Good Clinical Practice. The National University of Singapore Institutional Review Board (NUS IRB-Reference Code: B-15-016) gave ethical approval. This paper describes, according to SPIRIT guidelines, the trial design, setting, intervention and procedures that will be undertaken.

### Trial design

This interventional study will be a RCT comparing participation in a HT program to being in a waitlist control. The intervention will lasts for 6 months with 1-h HT sessions during the first 3 months followed by monthly sessions the next 3 months. Outcome assessments will be conducted at baseline, 3 months and 6 months. The 3-months follow-up intervals were decided based on a study by Gonzalez et al. which found that participants’ depressive symptoms declined after 3 months and these improvements were maintained in the final 6-month follow-up [6].

### Study participants

Seventy elderly will be recruited from a research center in the western district of Singapore. All interested and potentially eligible participants will be screened for cognitive status and other eligibility criteria.

English and/or Mandarin-speaking community-dwelling participants aged between 60 to 85 years and have a minimum score of 22 and above on the Montreal Cognitive Assessment (MoCA) will be enrolled into the study. The cut-off score of 22 on MoCA is to select participants who have intact cognitive impairment [22]. However, older adults will be excluded from the study if they have 1) history of severe psychiatric conditions e.g. schizophrenia, bipolar disorder; 2) dementia; 3) significant visual or hearing impairment; 4) marked upper and lower limb motor difficulties, which may affect their ability to participate in the study; 5) are currently suffering from or have history of severe medical conditions e.g. cancer, stroke, Parkinson disease; or 6) are participating in another therapy at the same time.

### Recruitment and baseline procedures

The flow of participants from recruitment to end of study is shown in Fig. 1. Potential participants who may fulfil the inclusion criteria will be invited to participate in the study. They will be contacted either through an invitation phone call or when they are at research centre for activities. The study will be explained in detail to potential participants with the participant information sheet (English and Mandarin versions available) before their written informed consent is obtained. They will be screened by trained research staff using MoCA and demographic questionnaire. Participants who meet the entry criteria will be enrolled into the study.

**Fig. 1 Fig1:**
[figure not shown]
Flow diagram of study protocol

Following successful screening, enrolled participants will proceed with the rest of the baseline assessments. The participants will be subsequently randomised into either the active treatment group or waitlist control. Utilizing the Random Allocation Software version 2.0 [23], randomization will be stratified by gender by the study-coordinator.

### Intervention

The HT intervention is delivered in 1-h sessions, weekly in the first 3 months, followed by monthly sessions for the next 3 months (see Table 1). The extension of monthly sessions for 3 months is to determine sustainability and longer-term changes. Conducted by a trained practitioner and volunteer facilitators, the intervention is designed to cultivate an interest in gardening and promote relaxation. The participants will be assigned into groups of 7 with a facilitator for enhanced personal engagement. The participants will be with the same group members and facilitator throughout the intervention in order to build rapport and social connectedness. The facilitators are volunteers with the National Parks Board, who were trained with some basic knowledge of horticultural skills such as plant propagation, plant identification, flower arranging, houseplant care, and horticulture crafts. The essential element of the HT program is to communicate to the participants that plants are living things that must be given care. This caring extends the emotional growth of the participants.

**Table 1 Tab1:** Planned activity sessions for the 6 months of intervention

Session	Topic	Activity	Venue
1	Introduction	1. Familiarisation with research centre 2. Group formation 7/group 3. Indoor Gardening basics	Research Centre
2	Introduction	1. Garden familiarisation 2. Vegetables growing brief 3. Sowing vegetables seedlings	Chinese Garden
3	Wetland Walk	1. Park amenities familiarization 2. Interpretive walk 3. Reflection	Sungei Buloh Reserve
4	Introduction	1. Briefing for vegetables maintenance 2. Weeding and fertilizing vegetables plot	Chinese Garden
5	Nurturing	1. Briefing on pressed flowers 2. Material preparation 3. Make pressed flowers card	Research Centre
6	Nurturing	1. Garden maintenance briefing 2. Weeding, pruning, mulching garden/vegetables	Chinese Garden
7	Colour Walk	1. Park amenities familiarization 2. Interpretive walk 3. Reflection	Singapore Botanical Gardens
8	Nurturing	1. Vegetables maintenance 2. Compost making brief 3. Make compost	Chinese Garden
9	Harvest and Cook	1. Harvest vegetables 2. Hands on preparation for food 3. Sharing of cooked vegetables	Research Centre
10	Harvest and Cook	1. Seed sowing 2. Herbal plant brief 3. Herbal plants propagation	Chinese Garden
11	Festive Walk	1. Park amenities familiarization 2. Interpretive walk 3. Reflection	Gardens by the Bay (Flower Dome)
12	Harvest and Cook	1. Community Garden tour 2. Plant care tips for herbs and plants that will be brought home 3. Reflection	Chinese Garden
13	Healing Walk	1. Park amenities familiarization 2. Interpretive walk 3. Reflection	Botanical Garden – Healing Garden
14	Gardening	1. Briefing 2. Create a culinary garden 3. Maintenance tips	Chinese garden – culinary garden creation
15	Nature Walk	1. Park amenities familiarization 2. Interpretive walk 3. Reflection	Gardens by the Bay (Cloud Forest)

Intervention sessions 1 to 12 will be conducted on a weekly basis while sessions 13 to 15 will be conducted once a month

Each session will start with breathing and stretching exercises, before going into the activity (Table 1). The stretching exercises improve the flexibility of the participants, giving them more freedom of movement for the HT activities. In the first 3 months of weekly sessions, the intervention comprises of 3 main components: 1) indoor horticultural activities, 2) park visits and 3) outdoor gardening. The indoor activities will include making pressed flowers, which is an extension of appreciation for nature, indoor gardening to encourage participants to engage in gardening activity at their home and take ownership of their own plants.

Participants will be brought on visits to various urban parks in Singapore such as the Singapore Botanical Gardens, Sungei Buloh Wetland Reserve and Gardens by the Bay. These visit tours will be facilitated by trained park guides who will share their knowledge on the plants and the landscapes with the participants. Participants will also be encouraged to engage themselves actively in the environment by paying attention to the sights and sounds in the nature parks, thereby appreciating the nature and sharpening their focus. Viewing of natural spaces has been found to reduce anger and increase positive affect, due to the restorative effects of nature [4, 5].

For the gardening activities, they will be held fortnightly at the Chinese Garden where participants will be taught to do weeding and seed sowing. Such active participation in the natural environment has been found to improve mood state where participants were less stressed and were invigorated by their experiences [7]. Vegetables such as ladyfinger, milk cabbage, and choy sum will be planted by the participants. They will be educated on the making of fertilizer as well as knowledge on herbal plants. When their vegetable crops are ready for harvest, the participants will be able to prepare a soup dish together to encourage social connectedness amongst them.

Throughout the intervention programme, there will be an emphasis on education and mental stimulation whereby the facilitation is structured in terms of a series of questions and answers. This encourages active discussion amongst the facilitators and participants and social engagement. Longitudinal studies on mental stimulation and socially integrated lifestyle in late life have been found to have beneficial effect on cognition [24]. In closing each session, participants are asked for their reflection and verbal feedback.

The waitlist control will be assessed at the same time-point as the active treatment group but will only receive the same intervention program 6 months later.

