### Sample size

For a pilot RCT with continuous outcomes, the recommended total sample size is 70, with 35 in each study arm with relative change in outcome variables within 95% confidence interval [41].

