### Biomarkers analyses and statistical analyses plan

In the analyses of the biomarkers, aliquoted plasma will be used to measure the cytokines and metabolic profiles of the research participants using single-analyte enzyme-linked immunosorbent assay (ELISA). Using targeted approach, selected RNA targets, which may include messenger RNA and micro-RNA, for a subset of the subject will be analysed based on the data obtained from the cytokines and metabolic profiles. Whole bloods aliquoted on Trucount tubes are stained with a series of fluorescence-conjugated antibodies marking the surface receptors of immune cell. Using flow cytometer, part of the phenotyping includes classical markers of senescence, Cluster of differentiation 57 (CD57) and Killer-cell lectin like receptor G1 (KLRG1), exhaustion of T cells, Programmed cell death protein 1 (PD1) and potentially identification of subpopulations of B cells and myeloid cells with a focus on the pro-inflammatory cells. The extent of DNA damage repair will be assessed by flow cytometry as well. Other immuno-assays aiming at identifying markers or predictors of immune status to examine the effects of the interventions may be applied with the bio-banked samples.

In the data analyses procedures, statistical significance level will be set at .05 for all descriptive and statistical analyses. All analyses will be performed using the SPSS. Based on the initial condition assignment and using the last observation carried forward (LOCF) method, intention-to-treat analyses will be conducted. Preliminary analyses will be performed next to assess the influence of demographic factors that (age, gender, education level, marital status, etc.). Where necessary, these variables will be included as covariates or control variables in the analyses. As some attrition is expected between interviews, prior to data analysis, comparisons will be made of retained and non-retained participants, to determine whether there are any systematic differences.

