If there are chance imbalances in baseline participants’ characteristics, they will be entered as covariates in the analyses. Repeated Measure Analysis of Variance (ANOVA) will be used to examine the difference of the outcome between the active treatment group and waitlist control group over the 3 time points [42]. If there are imbalances in baseline participants’ characteristics, those variables will be included as covariates in the analyses. Additionally, dependent t-test will be employed to analyse the changes in scores within the active treatment group across the 3 time-points.

Ratios of selected biomarkers will be taken between cortisol, IL-6, CRP and DHEA-S. Additionally, fold changes and percentage changes would be performed. In the case of significant difference between the baseline measurements of prognostic demographic variables, multivariate regression will be performed when examining the differences between the means of the biomarkers for the two study arms. Correlation and/or heatmap analyses will be carried out to examine the relationships between the biomarker levels. On the aggregate biomarker level, principal component analyses (PCA) will be performed to examine the overall effect of the treatment. Mediational analyses employing bootstrapping technique will be employed to explore the mediating variables between the psychometric outcomes and biomarker levels.

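### HT is given in fixed groups of 7, but the planned ANOVA and within-arm t-tests treat participants as independent; if outcomes correlate within groups, the 5% error rate is exceeded

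*Protocol article*

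**What the plan says.** Participants are randomised individually; the only restriction given is that "randomization will be stratified by gender by the study-coordinator". The HT arm is then divided: "The participants will be assigned into groups of 7 with a facilitator for enhanced personal engagement". The groups do not change: "The participants will be with the same group members and facilitator throughout the intervention in order to build rapport and social connectedness". Table 1 places group formation, 7 to a group, in session 1. The last paragraph of the Intervention section has the waitlist arm assessed at the same times but receiving the programme only 6 months later. The Sample size section states that "the recommended total sample size is 70, with 35 in each study arm".

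Under Biomarkers analyses and statistical analyses plan, the between-arm method is fixed: "Repeated Measure Analysis of Variance (ANOVA) will be used to examine the difference of the outcome between the active treatment group" and the waitlist group over the 3 time points. Dependent t-tests follow, for change within the active arm. The level is also fixed: "statistical significance level will be set at .05 for all descriptive and statistical analyses". The adjustments named for these tests are demographic factors and baseline characteristics that turn out imbalanced. No therapy-group or facilitator effect, ICC or design effect appears in the sample size or analysis text.

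**The concern.** Randomising individuals makes participants independent at entry, but the HT arm is not treated individually. Seven people share one facilitator and the same companions for 15 sessions, and the article presents that shared experience as part of how HT works. Two members of one group may therefore end up more alike than two members of different groups. Waitlist participants have no such tie before 6 months, so the design is partially nested: clustered in one arm only.

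Both named tests take their standard error from the spread between individuals. If there is real variation between groups, that error term is too small, confidence intervals are too narrow and the .05 level is not the true error rate. The exposure is clearest for the Friendship Scale, because social connectedness is both a stated purpose of the fixed groups and an outcome. Self-reported mood and well-being come next. The dependent t-tests are hit harder than the ANOVA, because every participant in them is clustered.

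**Working it through.** **Plan's own figure.** The total of 70 cannot be re-derived: no effect size, standard deviation or power is given, only a pilot-trial recommendation "with relative change in outcome variables within 95% confidence interval".

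**Inputs from the article.** Group size m = 7; 35 per arm, so 35/7 = 5 HT groups; level 0.05, taken as two-sided because sidedness is not stated.

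**Assumed input.** The within-group ICC is not given, so a range of 0.01 to 0.20 is shown.

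**Formulas**
- Design effect (DE) in the HT arm: DE = 1 + (7 − 1) × ICC. In the waitlist arm it is 1.
- Effective HT sample: 35/DE.
- True over reported standard error between arms, equal arms: √((DE + 1)/2).
- True over reported standard error within the HT arm: √DE.
- Actual type I error: 2 × (1 − Φ(1.96/ratio)).

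Example at ICC 0.10: DE = 1 + 6 × 0.10 = 1.6. The between-arm ratio is √(2.6/2) = 1.140 and the error is 2 × (1 − Φ(1.96/1.140)) = 8.6%. The within-arm ratio is √1.6 = 1.265 and the error is 12.1%.

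| ICC | DE | Effective HT n | SE ratio, between | Error, between | SE ratio, within HT | Error, within HT |
|---|---|---|---|---|---|---|
| 0.01 | 1.06 | 33.0 | 1.015 | 5.35% | 1.030 | 5.7% |
| 0.05 | 1.30 | 26.9 | 1.072 | 6.8% | 1.140 | 8.6% |
| 0.10 | 1.60 | 21.9 | 1.140 | 8.6% | 1.265 | 12.1% |
| 0.20 | 2.20 | 15.9 | 1.265 | 12.1% | 1.483 | 18.6% |

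**Check by simulation.** Null trials had 5 groups of 7 against 35 independent controls: 40,000 runs for the t-tests and 20,000 for the ANOVA. For the ANOVA, the within-person correlation was set at 0.5, and the group effect was absent at baseline and equal at 3 and 6 months.

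| ICC | Two-sample t-test | Group-by-time F test | Within-HT t-test | Group means, Satterthwaite df |
|---|---|---|---|---|
| 0.01 | 5.1% | 5.2% | 5.5% | 4.9% |
| 0.05 | 6.7% | 6.6% | 8.5% | 5.3% |
| 0.10 | 8.7% | 8.4% | 12.2% | 5.4% |
| 0.20 | 12.3% | 12.8% | 19.0% | 5.5% |

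At ICC 0 the group-by-time F test rejects 5.1%, so the excess comes from the clustering. The last column compares the 5 HT group means with the individual waitlist values and stays close to 5%.

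**Where the group effect must sit.** Groups form after randomisation, so they can affect only the later measurements. A random intercept that is constant over time adds the same amount to a person's baseline, 3-month and 6-month values. It drops out of every difference over time and leaves the group-by-time test uncorrected.

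**The case against.** The strongest reply is that everything depends on an ICC the article does not give. At 0.01 the excess is a fraction of a percentage point. Table 1 lists one activity and one venue per session with no variation by group, which limits how far groups can diverge. Nothing in the article points to sizeable group correlation in blood pressure, weight, blood markers or neuropsychological scores. This stands. A reader might infer that type I error certainly exceeds 5% and that every between-arm interval is too narrow. The article does not support that; the inflation is conditional and likely to differ by outcome.

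A reader might also infer that all the tests wrongly treat 70 people as independent. The ANOVA uses 70; the dependent t-tests use only the 35 in the HT arm.

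A third inference would be that clustering invalidates the sample size. The 70 is presented as a pilot recommendation with no power claim, so no stated figure is contradicted.

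It can also be said that a condensed article may leave the random-effects structure to an analysis plan. That would carry weight had the article been silent, but it names its tests, and those tests do not match the way it delivers the treatment. The pilot label does not remove the problem either, since the article states directional hypotheses and a .05 level.

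**Conclusion.** The concern holds in conditional form. The named analyses assume independence, while the delivery of HT gives good reason to expect some correlation within groups in one arm. If that correlation is positive, reported standard errors are too small: by a factor of about 1.07 to 1.26 between arms and 1.14 to 1.48 within the HT arm for ICCs of 0.05 to 0.20. The nominal 5% then becomes about 6.8% to 12.1% between arms and 8.6% to 18.6% within HT. At 0.01 it is of no practical importance.

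These figures assume 5 full groups of 7, equal arms, no dropout and a two-sided test. They also assume that the groups and facilitators stand for those that HT would have elsewhere, in line with the Discussion's aim of guiding later trials and wider programmes.

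One limit cannot be removed by analysis. Each group keeps one facilitator, so facilitator and group effects are inseparable. A cluster-aware model allows for their combined variation but does not say which is responsible.

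**What to change.** In Biomarkers analyses and statistical analyses plan, replace the independence-based tests as follows.

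- **Between arms:** a partially nested mixed model with a random therapy-group effect in the HT arm only. Place it on the post-baseline measurements or on change from baseline, not only as a constant intercept. Treat each waitlist participant as a singleton, allow arm-specific residual variance, and use Satterthwaite or Kenward-Roger degrees of freedom.
- **Check:** compare the 5 HT group mean changes with the individual waitlist changes, using Satterthwaite degrees of freedom.
- **Within HT:** apply the same group-aware approach in place of the plain dependent t-tests.
- **Reporting:** give the ICC for each outcome, noting that 5 groups estimate it imprecisely. Social connectedness and self-reported mental health have priority.

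**Cost.** No new recruitment or measurement is needed: Study progress says data collection is complete and analyses are under way. A group identifier must be in the research database. Data management does not list one, so it would have to come from session assignment, on the assumption that those records were kept.

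The statistical price is real. In simulation the group-mean intervals were on average about 16%, 26% and 43% wider than the naive ones at ICC 0.05, 0.10 and 0.20. An ANOVA-type equivalent of the mixed model estimated the group variance as zero in 42%, 31% and 17% of trials. Its error rates were 4.1%, 4.4% and 5.1%, so it is somewhat conservative when the ICC is low.
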